### Aims and objectives

Within the context of primary care and the five most common musculoskeletal presentations, there are two key aims of the KAPS: 1) to refine and externally validate the draft Keele STarT MSK tool, and 2) to explore how such a tool might best be implemented within clinical practice. Specific objectives include:
refine the Keele STarT MSK tool based on face, discriminant, construct, and predictive validitydetermine the tool risk-strata cutoff points based on optimal predictive values and suitability for matched treatment optionsestimate the proportions of patients classified at low, medium, and high risk of poor outcome and describe their characteristics, including patient health care utilization and costs and health-related quality of lifeexamine the validity of a refined tool (predictive, external validation)explore clinicians’ perspectives on the acceptability and “added value” of stratified care based on prognosis compared to current primary care management of patientsexplore patients’ perspectives about stratified primary care based on prognosis (eg, patient subgrouping using the tool, matched treatment options)identify clinicians’ and patients’ perceived barriers and solutions to using the draft Keele STarT MSK tool and matched treatment options in clinical practice.

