The predictive performance of the draft Keele STarT MSK tool will be investigated by assessing the ability of the tool to predict outcome at the 2-month follow-up. It is hypothesized that participants with lower baseline scores (ie, those at “low” risk (or “medium” risk compared to “high” risk) will have better outcomes. Evaluation will be based on analysis of variance using linear constraints for numerical 2-month measures, and the *χ*^2^ test for trends for comparing and testing associations in categorical 2-month outcome measures. In relation to the key outcomes of physical health (SF-36-PCS), predictive performance of the draft tool will be expressed in terms of percentage of variance explained (parametric and nonparametric Nagelkerke *R*^2^), calibration (calibration slope and Hosmer–Lemeshow test), and area under the receiver-operating characteristic curve (*C*-statistic) via receiver-operating-characteristic analysis for discrimination, including dichotomies for the SF-36-PCS based on lower tertiles extracted from a similar cohort,^26^ ie, 37.17 and 39.61 at 2- and 6-month follow-up, respectively.^55^,^56^ A replication of this analysis using the SF-36-PCS will be carried out for pain intensity (eg, a score of 5 or more denotes moderate/severe pain).^57^ In addition, as a sensitivity analysis, variation in performance will be examined across participants with different index pain sites.

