Second, opportunities to refine and improve upon the draft Keele STarT MSK tool will be investigated. In particular, face and content validity, completion rates, and predictive performance of the tool will be optimized by the inclusion of additional or alternative items or the removal of items. Predictive performance will be assessed against physical health (SF-36-PCS) and pain-intensity scores at 2-month follow-up. Primary evaluation will use the whole sample, but sensitivity analyses will be carried out for participants with pain at each index site. A number of single-candidate item questions will be included in baseline questionnaires (physical, psychological, or social factors); these are based on an updated review of prognostic factors for musculoskeletal pain in primary care, overview of other comparable tools (Örebro and Von Korff risk score), and examination of other questions used to measure the same and/or other identified key domains. As with the development of the Keele STarT Back tool,^23^ all candidate items will be potentially modifiable by treatment. This analysis will be carried out in stages by substituting, adding, or removing one item at a time. Decisions about whether to change, add, or remove an item will be based on all available information (face and content validity, item-completion rate, and predictive performance overall and across pain sites). For example, if swapping one item in the draft tool for a new candidate item with better face validity leads to similar item-completion rates and improves predictive performance compared to the draft tool, a decision would be made to remove the existing item and add the new item.

The refined tool will then be investigated to see whether it is exhaustive by checking whether items reflecting different domains can be added to improve predictive validity substantially. In addition, the potential for item redundancy will be examined by reviewing the tool’s predictive performance versus simplification by exclusion of single items one at a time. At all stages, the main focus will be on improved predictive performance across the total study population, but review of predictive validity will also be extended to individual index pain sites, and face and construct validity will be taken into account.

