The third step is to identify tool risk-strata cutoff points. Two approaches will be considered. One approach will identify the optimal cutoff points on the 0–9 scale that stratifies the population into three subgroups of low, medium, and high risk based on evaluation of sensitivity/specificity, predictive values (positive/negative), and likelihood ratios (positive/negative) against clinical thresholds for the SF-36-PCS and pain, as detailed earlier. An alternative method used in the development of the STarT Back tool^23^ is based on a separate cutoff point using a psychosocial subscale to identify complex patients. In this approach, items that could be classified as key in identifying patients who are at high risk (ie, psychosocial, complex problems) will be identified. These two approaches to defining cutoff points will be compared in terms of discriminant, construct, and predictive validity (as described in steps 1 and 2) and reviewed by the study team for feasibility and fit.

The fourth and final stage is to determine whether the refined version of the tool has external validity. This will be done by assessing the discriminant, construct, and predictive validity of the refined tool against 6-month outcomes. In addition, these same analyses will be conducted following multiple imputation of missing data to assess robustness of the tool’s properties. At all stages of the analysis, a clinical advisory group and user representatives (patient and public involvement of people with similar musculoskeletal conditions) will be consulted about the draft versions of the Keele STarT MSK tool, and any suggested changes will be discussed, to ensure acceptability, face validity, and clinical utility of the final screening tool, cutoff points, and identified risk strata.

Current health care and treatments for the whole cohort by risk strata and by pain site will be described using data from patient self-report questionnaires at 6 months. NHS and non-NHS resource use will be multiplied by unit costs obtained from standard sources, in order to calculate mean overall per patient costs and by broad health care-resource use type. A description of mean costs by risk strata and by pain site will be presented. Responses to the EQ-5D-5L will provide estimates of mean quality of life (utility) values, again for the whole patient group and by risk strata and pain site.

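### For the refined tool, stage four is internal validation at a later time point in the development cohort, not external validation

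*Protocol article*

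**What the plan says.** Under Aims and objectives, the first key aim is "to refine and externally validate the draft Keele STarT MSK tool". A separate objective in the same list is to examine the refined tool's validity, and it names external validation explicitly.

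Cohort study analysis then sets out four stages in one cohort:

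- **Stage one** describes the draft tool as it stands, including its prediction of 2-month outcome.
- **Stage two** refines it by substituting, adding or removing items one at a time. "Predictive performance will be assessed against physical health (SF-36-PCS) and pain-intensity scores at 2-month follow-up". On the sample: "Primary evaluation will use the whole sample, but sensitivity analyses will be carried out for participants with pain at each index site". On the source of new items: "A number of single-candidate item questions will be included in baseline questionnaires".
- **Stage three** chooses the risk-strata cutoffs "against clinical thresholds for the SF-36-PCS and pain, as detailed earlier". The SF-36-PCS thresholds given earlier in that section are "37.17 and 39.61 at 2- and 6-month follow-up, respectively".
- **Stage four**: "The fourth and final stage is to determine whether the refined version of the tool has external validity". The data for this are the same cohort's 6-month outcomes, and the analyses are repeated after multiple imputation.

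Cohort study sample size counts all 1,250 expected 6-month respondents towards a minimum of 100 per risk subgroup, which it says external validation requires.

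**The concern.** External validation asks how a finished tool performs in people who played no part in building it. Here the people who selected the items and cutoffs are the people on whom the refined tool is then judged. Moving the outcome from 2 to 6 months tests a longer horizon, which is useful, but it brings in no new patients, practices or setting.

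Two things follow. First, the label promises evidence on transportability that stage four cannot give. Second, some chance advantage from item selection can carry over: an item that happened to fit these patients' 2-month outcomes will also tend to fit their correlated 6-month outcomes.

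The label matters because the Abstract promises a validated tool with established cutoffs, and the Discussion says the tool is already in use in a planned cluster trial. Readers will take the 6-month figures as evidence of performance elsewhere.

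**Working it through.** **1. The plan's own figures reproduce.** Inputs are from Cohort study sample size.

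- Baseline: 3,000 × 0.60 = 1,800.
- Retention implied by 1,250 at 6 months: 1,250 / 1,800 = 69.4%.
- High-risk respondents at the stated 10% floor: 1,250 × 0.10 = 125, against the required 100.

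The 125 is reached only if every 6-month respondent is a validation patient. No respondent is then left outside the development sample.

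**2. What differs between refinement and stage four.**

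- Patients: the whole sample in stage two; the same cohort in stage four.
- Practices: the same.
- Predictors: candidate items are described only for baseline questionnaires, so stage four must, by inference, score the same baseline answers. (Table 1 lists the draft tool, but not the candidate items, at all time points.)
- Construct comparators: Table 1 lists the Örebro short form and the STarT Back tool at baseline only, so this part of stage four also reuses baseline data.
- Outcome: 2 months, then 6 months. This is the only change.

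**3. Would a hold-out rescue the label?** At the 10% floor, holding out a fraction f leaves 125 × f high-risk respondents.

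- f = 1/2: 62.5
- f = 1/3: about 42
- f = 1/4: about 31

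All are below 100. Reaching 100 needs f = 100/125 = 80%, which leaves 250 respondents for refinement. A separate cohort would need 100/0.10 = 1,000 completers, or 1,000/0.694 = about 1,440 at baseline. A random split would in any case draw on the same practices.

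**4. How large might the optimism be?** The article gives no number of candidate items and no correlation between the two outcomes, so both are assumed. Two simulations of one-at-a-time swaps on 2-month C in 1,250 patients with a nine-item score give a range.

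*Simulation A*: 10 further candidates, poor outcome = worst third, 30 runs per setting. The 2- and 6-month residuals are √ρ·e + √(1−ρ)·u, with e shared and u separate, so their correlation is ρ. The selected tool's 6-month C was compared with that in 20,000 new patients:

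| ρ | 2-month C, same patients | 6-month C, same patients | 6-month C, new patients | 6-month optimism |
|---|---|---|---|---|
| 0 | 0.724 | 0.699 | 0.700 | −0.001 |
| 0.5 | 0.719 | 0.701 | 0.699 | 0.002 |
| 0.8 | 0.722 | 0.710 | 0.700 | 0.010 |

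The Monte Carlo standard error of the last column is about 0.003, so only the value at ρ = 0.8 stands clear of zero.

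*Simulation B*: 15 interchangeable candidates so that no swap truly helps, up to four swaps, ρ = 0.5 to 0.7, 25 runs per setting. This measures the gain over the draft tool. The apparent gain was 0.017–0.018 at 2 months, 0.007–0.008 at 6 months in the same patients (standard error about 0.0015), and 0.000 in new patients.

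Together they put the optimism at about 0 to 0.010 in C, rising with the correlation between the outcomes. Neither covers cutoff selection or transfer to other practices.

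**The case against.** There is a good case for a narrow reading, and most of it stands.

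- **The draft tool.** The headline aim and the closing sentence of the sample-size section speak of the draft. Background reports that the draft was assessed in two other data sets, from physiotherapy and interface services. Testing it unchanged in general-practice patients is external in a proper sense. A reader might infer that nothing in the study is external; the documents do not support that. The objective on the refined tool and stage four remain wrongly labelled.
- **Cutoffs and 6-month data.** Because the stage-three cross-reference reaches both SF-36-PCS thresholds, a reader might infer that cutoffs will be tuned on the validation outcome. The Abstract places refinement at baseline and 2 months and validation at 6 months, and stage three compares its two approaches by reference to steps 1 and 2, which use 2-month outcomes. What is left is a loose cross-reference.
- **No optimism correction described.** The article condenses a fuller protocol, and any analysis plan is not shown. The silence is no fault in itself; the correction belongs in the fix because the label has to change.
- **Small numerical effect.** The simulated optimism is at most about 0.010, and real decisions will also weigh face validity, completion rates and advisory-group input. This stands. It also means that one should not say the 6-month results tell us nothing about new patients: in the simulations the same-patient and new-patient values lay close together.
- **Further validation is foreseen.** The Discussion anticipates it, but its stated limitations do not mention the reuse of the sample.

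**Conclusion.** The point holds for the refined tool. One objective and stage four claim external validation, while the design supplies internal validation at a later horizon in the development cohort. No analysis of this cohort alone can make it external for a tool refined on all of it.

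The main consequence is for what may be concluded: performance in other patients and settings is untested. The numerical consequence is probably modest, about 0 to 0.010 in the 6-month C-statistic. That range rests on an assumed number of candidate items, an automated swap search and residual outcome correlations of 0 to 0.8, none of which the article states. Optimism from cutoff selection is unquantified. That stage four scores baseline answers is an inference from where the candidate items are collected.

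**What to change.** 1. **Relabel.** In the refined-tool objective, in stage four, and in the sample-size section where it supports stage four, describe the step as internal validation against 6-month outcomes in the development cohort. Keep the word external for the unchanged draft tool only. Add the reuse of the sample to the limitations in the Discussion.
2. **Close the cross-reference in stage three.** Name the 2-month thresholds (37.17 for SF-36-PCS, and the pain threshold applied at 2 months), in line with the Abstract, so that items and cutoffs are fixed before 6-month outcomes are used.
3. **Correct for optimism.** Report the 6-month C-statistic, R² and calibration with a bootstrap correction that repeats the data-driven part of the item and cutoff search, and say that judgement-based choices are not captured. Leave-one-practice-out validation is an alternative only if the number of practices, which the article does not state, allows it.

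The cost is changes of wording, some analyst time and slightly less favourable headline performance. No new data are required.

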### Qualitative study

Focus groups will be conducted with patients, GPs, and other HCPs. The key aims of the focus groups for GPs and HCPs are to investigate clinicians’ perspectives on the “added value” of prognostic stratified care to current primary care management of patients who consult for musculoskeletal conditions and to identify practical implications of embedding the Keele STarT MSK tool within consultations that complement existing diagnostic approaches. For patients, the key aim is to explore their views on the most acceptable ways of communicating prognostic screening results and the understanding of a stratified model of care. For both GPs/HCPs and patients, there is also the aim of understanding any potential barriers and exploring practical solutions to the use of stratified care. If difficulty is experienced in recruiting an adequate number for the focus groups, we will conduct one-to-one interviews (face to face or over the telephone) with respondents who have expressed an interest in taking part, but have not been able to attend any of the arranged focus groups, and who agree to this alternative data-collection method.

#### Patient focus groups (and interviews)

A subsample of patients who have responded to the cohort baseline questionnaire, given consent to further contact, and provided telephone contact details will be invited to take part in a focus group. Patients will be purposively sampled to obtain a sample with diverse characteristics; including, age, socioeconomic status, and reported pain site/severity. Such information will be obtained from patients’ participation and information given in the cohort study questionnaire. We plan to convene approximately two patient focus groups (up to eight patients per group), but the final number will be determined by “data saturation” (if all themes have been explored in sufficient depth). Patients who express interest in taking part will be posted a formal invitation letter and participant information sheet. After sufficient time (approximately 2–3 days) for potential participating patients to receive and read the information and to decide whether or not to take part, patients will receive a further telephone call/s to confirm agreement and make arrangements. A date will be agreed upon, based on convenience to all patients and researchers, and a final confirmation letter of the date, time, and venue (including directions and map) will be sent to participating patients by post. Patient focus groups (and interviews) will be convened at a convenient location and setting, such as Keele University or another potential venue, such as a GP practice, other local NHS site, or the patient’s own home. Written consent will be obtained prior to the focus group discussion or one-to-one interview (as appropriate). Patients who agree to a telephone interview will receive a consent form along with their confirmation letter, and will be instructed to return it to the study team within a prepaid envelope.

#### General practitioner focus groups (and interviews)

We will invite GPs from participating practices plus GPs from known clinical networks to attend a focus group. Although no purposeful sampling will take place for the recruitment of GPs or HCPs, the study will consider a range based on experience levels and length of time in practice, as well as varying degrees of familiarity with a prognostic approach to stratified care for low-back pain. We will hold approximately four focus groups (up to eight GPs per group), though the final number will depend on data saturation. One-to-one interviews either face to face or via the telephone will be carried out as appropriate (where recruitment to focus groups has not provided an adequate sample size) and where practically possible for GPs who cannot attend a focus group. Focus groups will be held at Keele University or alternatively at one or more of the participating practices, dependent on preferences. One-to-one interviews will be conducted at a location convenient to the participating GPs, such as their practice. All GPs invited to take part will receive invitation letters and information sheets. Written consent will be obtained immediately prior to the focus-group discussion (or interview).

#### Health care professional focus groups (and interviews)

Approximately two focus groups will be convened with other HCPs (eg, such specialists as orthopedic surgeons, pain specialists, rheumatologists, and physiotherapists). However, the final number of focus groups will be dictated by data saturation. HCPs will be recruited from the services linked to participating GP practices and other known clinical networks. All HCPs will receive an invitation letter and information sheet, and written consent will be obtained immediately prior to the focus-group discussion (or interview). Focus groups (and one-to-one interviews) will be convened at either Keele University or at a convenient NHS or community venue.

#### Data collection

Each focus group will be convened in a similar way. First, a short presentation by the study team, including a summary and explanation of stratified primary care, will be delivered, followed by questions from participants in the focus groups. The presentation will include examples (vignettes) of how the Keele STarT MSK tool might be used in clinical practice and how patients might be classified into low-, medium-, and high-risk subgroups. Following the vignettes, there will be group discussion based on the topic guide, where participants will discuss each case scenario and share their views of the advantages and disadvantages, as well as the added value, face validity, acceptability, and appropriateness of stratified care for their particular pain problem (in the case of patients), and for use within clinical practice (for GPs/HCPs). One-to-one interviews will follow the same process, with a short explanation of stratified primary care, presentation of vignettes, and discussion based on the topic guide. Key emergent insights will be incorporated into the topic guides and explored in subsequent focus groups and interviews. This process is common to qualitative research, and facilitates the development of new insights not hitherto anticipated.

#### Sample size

For patients, we anticipate a 50% response rate, and so will contact approximately 32 patients, with the aim of 16 patients agreeing to take part in focus groups or interviews. We aim to recruit to four GP focus groups (up to eight per group, so a total of up to 32 GPs) and two HCP groups (up to eight per group, so a total of 16 other HCPs).

#### Study analysis

Focus-group and interview data will be transcribed and coded thematically using NVivo qualitative data-management software. Members of the research team, including social scientists and clinicians, will independently code a sample of the transcriptions and discuss their interpretations at regular meetings. Each focus group and interview will be analyzed thematically in search of similarities and differences in clinicians’ and patients’ views about the face validity, acceptability, and added value of prognostic screening linked with matched treatment options in the care of patients with musculoskeletal pain.

The qualitative data will in turn be analyzed in search of common themes using the constant comparative method,^58^ in order to identify the perceived barriers and solutions to using stratified care in clinical practice for the management of patients with the five most common musculoskeletal pain presentations. Specifically, the analysis of focus-group and interview data will be underpinned by Michie et al’s^59^ “theoretical domains framework”, previously applied to behavior change and implementation in health care settings.^60^,^61^ The framework contains 14 domains, including social, psychological, behavioral, and environmental, across which we will map the qualitative findings to determine the most salient influences on the potential for adoption of stratified primary care in practice. The analysis of the domains will help to identify the key barriers and enablers to stratified care, and identify key attributes (eg, skills, beliefs, knowledge, professional identity, environmental context), in order to address barriers or facilitate key enablers to change in future phases of the wider program of our research.

